### Sample size

We aim to recruit 50 patients into the study in 2 years. This sample size is based on comparable feasibility studies.^28 29^

### Data analysis plan

#### Patients and HCPs’ experiences with CopA

Quantitative data collected through the MIDI and GEMS questionnaires will primarily be analysed using descriptive statistics. The MIDI results will be used to identify key implementation determinants, highlighting the most frequently cited factors that facilitate or hinder the implementation process. Mean scores per determinant will be calculated. A higher mean score indicates that an HCP perceives this determinant less as a barrier to implement CopA; higher scores are associated with higher expected levels of use.^30^ Differences between implementers and non-implementers will be assessed.

The GEMS questionnaire will provide insights into patients’ perceived usability and satisfaction with remote monitoring. In order to calculate the GEMS score, all items of the GEMS must be completed. In order to calculate the GEMS score, all items of the GEMS must be completed. To calculate participants’ satisfaction score, Likert scales of the GEMS questions will be revised from a 10-point to a 5-point scale, with values of 10 and 9 revised to 5, and 8 and 7 revised to 4, respectively, with higher scores indicating higher satisfaction. This adjustment was made for comparison of the items and to maintain consistency with the other items of the GEMS Satisfaction subscale. In order to calculate the subscale and overall GEMS scores, positively framed items from the GEMS were calculated in line with other usability metrics.^26^ Reversed items were calculated by subtracting the score from 5 (5-Score). Higher scores indicate better usability and satisfaction, with higher values reflecting more favourable perceptions of the system’s usability. The total GEMS score could reach a maximum score of 36 (100%) and was normalised by dividing the raw score by 36 and multiplying the score by 100.

#### Identification of barriers and facilitators to implementation

This study will generate qualitative data from interviews and focus groups with patient participants and HCPs at our clinic. These data will be analysed using reflexive thematic analysis based on the methods described in Braun and Clarke.^31^ Reflexive thematic analysis positions meaning as constructed through language and context. Two researchers (one junior and one senior researcher) will conduct line-by-line inductive, semantic coding using MAXQDA. Importantly, these researchers are not involved in ovarian cancer follow-up care and are not direct colleagues of the HCPs participating in this study, warranting an objective view. Both researchers independently perform this initial coding, whereafter they review the codes together and reach consensus on the final list of codes. Themes will be constructed to capture patterns of barriers and facilitators of the intervention in clinical practice on repeated, reflective engagement with the data. After these themes are developed, discussions with the broader research team, including two patient representatives, a clinician and implementation specialist, will take place contributing to critical interpretation of the constructed themes. The analysis and reporting of these findings will follow the Consolidated criteria for Reporting Qualitative Research.

#### Process evaluation of CopA

The quantitative data will be analysed using descriptive statistics such as calculation of proportion, frequencies, means and SD for all the aspects of the first four process measures.

### Patient and public involvement

Focus groups with patients with ovarian cancer^7^ and our patient sounding board taught us that the organisation of follow-up care needs change. Patients expressed a need for more self-management and more personalisation, leading to the idea for this project. During the development of CopA, two patient representatives were involved and repeatedly asked for feedback on the design of CopA as well as the implementation strategy in clinical care. They also reviewed the patient leaflets and online patient information to check that the language was suitable. A lay summary of our study findings will be developed and disseminated through Olijf, the patient organisation for women with gynaecological cancer.

### Ethics and dissemination

This study conforms to the Declaration of Helsinki. The medical ethical review board of Amsterdam University Medical Centres exempted this study from further assessment (METC 2022.0256) as this study was not subject to the Dutch Medical Research Involving Human Subject Act and approved the study protocol. In case of changes to the protocol during the study, these will be communicated to the ethics committee. The study is partially funded by a Clinical Fellow Grant from ZonMw (grant number 09032212110039; personal grant awarded to [name]). The funder will not be involved in data analysis or report writing. Participant confidentiality will be ensured by anonymising outcome data by using identification numbers in data analysis. Interviews and focus group discussions will be led by researchers, not directly involved in care of participants. In Dutch national guidelines regarding follow-up care after ovarian cancer, it is stated that patients are allowed to choose their preferred route of FU, ranging from no regular appointments to phone consultations only to 3 monthly hospital visits. Studies have shown that omitting regular hospital visits does not affect oncological outcome.^29^ Therefore, there are no risks involved with regard to participation in this study. Nonetheless, each participant has the possibility to stop the study at any time and return to the standard follow-up protocol. At the end of the study period of 2 years, each participant will be asked to keep access to the home monitoring platform or, if they prefer, to return to standard care. The findings of this study will be published in peer-reviewed journals, presented at relevant conferences and disseminated to the public via newsletters of patient association for gynaecological cancer Olijf and through website and social media channels of ZonMw and Amsterdam University Medical Centers. All outputs will be authored and approved by the research team. Access to the full protocol including all measurement instruments and questionnaires used is available on request to the corresponding author. The principal investigator (ie, [name]) declares no financial or competing interests.

## Discussion

This feasibility study will provide valuable insights into the implementation of remote monitoring using PROMs combined with home measurement of weight and waist circumference as an alternative to regular hospital visits for follow-up in patients with ovarian cancer. We will evaluate experienced usability and satisfaction from both the patients’ and HCPs’ perspectives, combining it with a process evaluation.

A strength of this study is that PROMs are already integrated into current workflows, so both patients and HCPs are familiar with the questionnaires and online patient portal. Another strength is the mixed-methods design in which we combine validated measurement instruments to assess feasibility and qualitative methods to gain more in-depth insight into their experiences. The process evaluation will guide further implementation efforts.

Some limitations should be mentioned as well. Although we do not select patients on having sufficient digital skills, the voluntary nature of participating in this study may introduce a selection bias, as it might scare patients who struggle with technical applications. Consequently, the findings may not fully represent the usability and satisfaction across the entire population. Another limitation of the study is the requirement for Dutch language proficiency, which may also exclude a portion of the patient population and affect the representativeness of the sample. Additionally, the fact that it is a single centre study may also negatively affect the generalisability of the results.

Future studies are needed to assess the actual impact of this form of follow-up care on patient outcomes, such as oncological outcomes, quality of life and costs.

In short, the findings of this study will provide valuable implementation lessons for remote monitoring in ovarian cancer follow-up care using PROMs, potentially offering patient-centred care to these women.

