### Patient population and in- and exclusion criteria for CopA

This study is aimed at all patients who received primary curative treatment for ovarian cancer (all FIGO (i.e. International Federation of Gynecology and Obstetrics) stages) and receive FU care. Patients will be included if they are within the first 2 years after the end of primary treatment. A small group of patients who receive maintenance therapy (with poly-ADP-ribose-polymerase inhibitors) will be excluded from this study, as they receive a different FU care plan with regular blood tests, scans and examinations at the outpatient department.

Patients are eligible for participation if they meet the following criteria: (1) completion of primary treatment for ovarian cancer less than 2 years ago, (2) having Internet access and sufficient degree of digital literacy as estimated by a HCP, (3) ≥18 years old and (4) ability to use the patient portal (MyChart). Patients are ineligible once they have a recurrence or if they lack sufficient proficiency in Dutch, since the patient portal is currently only available in Dutch.

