### Patient recruitment for this pilot study

Patients are assessed for eligibility by their HCP involved with their treatment and FU care. Eligible patients who ended primary treatment will be given the choice to either receive this alternative form of FU care (ie, CopA) or proceed with the standard 3-monthly FU care, as currently employed in our region. Patients who are willing to participate will be informed about CopA by their HCP and case manager (ie, oncological nurse). They may always change their decision and return to standard 3 monthly FU care. Specific patient information (patient leaflets and short video clip) will be developed to support patients in decision-making. Informed consent will be obtained by their lead physician.

After obtaining informed consent, the case manager provides the participant with the instruction about the monitoring and a measuring tape to measure waist circumference at home. Patients are instructed to use their own weighing scale. Patients will receive a video and a website link including detailed information and explanation about CopA. The research team will be available to provide technical assistance for the duration of the study. Importantly, at the start of the study, it is emphasised that if patients need medical attention, they should contact the hospital by telephone at all times. Patients who experience a recurrence of disease during the study period will no longer participate in the home monitoring programme as they require a different type of care and treatment.

Recruitment started in November 2024 and to date 26 patients have been included in the study. Anticipated end date of the study is mid 2027.

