##### Reach

Reach concerns the degree to which an intended audience participated in the intervention. The research team identifies from the EHRs which patients finish treatment for ovarian cancer and enter follow-up. We register what proportion of these patients decides to participate in the study and who declines. Reasons for exclusion will be registered, as well as the number and reasons for drop-out during the study.

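### The limitations deny selection on digital skills, but eligibility requires HCP-judged digital literacy and portal ability, so the usability and satisfaction results apply only to women judged digitally able

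*Protocol article*

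**What the plan says.** Three places in the protocol article bear on this point.

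- **Patient population and in- and exclusion criteria for CopA.** The second criterion is "having Internet access and sufficient degree of digital literacy as estimated by a HCP". The fourth is that the patient can use the MyChart portal.
- **Patient recruitment for this pilot study.** "Patients are assessed for eligibility by their HCP involved with their treatment and FU care". Patients found eligible are then offered a choice between CopA and standard 3-monthly follow-up.
- **Discussion, limitations.** "Although we do not select patients on having sufficient digital skills", the text begins, and it goes on to say that "the voluntary nature of participating in this study may introduce a selection bias" because patients who struggle with technology may be put off. It concludes that "the findings may not fully represent the usability and satisfaction across the entire population".

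The same paragraph of the Discussion names the Dutch-language requirement as an exclusion that affects representativeness, and adds the single-centre setting. It does not name the digital-literacy or portal criteria.

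**The concern.** The limitations paragraph describes a study without a digital-skills screen, whereas the eligibility section describes one with such a screen. Both texts are current.

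The trait matters because it is so close to what is measured. The abstract explains feasibility as usability and satisfaction, and the patient instrument, GEMS, asks how usable and satisfactory a home self-monitoring tool was. The women most likely to find a portal hard to use are those whom an HCP would judge insufficiently digitally literate, and they are removed before consent.

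A reader who relies on the Discussion would think that such women had been offered CopA and had stayed away by choice. A later centre could then take the usability scores and the list of patient barriers as coming from a group that was open to patients of any digital skill.

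**Working it through.** No arithmetic applies. The article gives no figure for the share of patients excluded on digital grounds, and the target of 50 patients rests on comparable feasibility studies and not on a formula. The check is a comparison of passages.

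1. **Is there a digital-skills screen?** Yes. Criterion 2 requires a sufficient level of digital literacy and criterion 4 requires ability to use the portal. Both are conditions for entry.

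2. **Who applies it, and when?** The treating HCP, at the eligibility assessment. The choice between CopA and standard care is offered only to eligible patients, so the screen comes before any self-selection.

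3. **What does the Discussion say about it?** It says there is no selection on digital skills, and it gives voluntariness as the route by which digitally less able patients may be missing. That is a different mechanism: a patient who declines was offered CopA, while a patient who is screened out was not.

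4. **Which results are affected?**
   - GEMS at 6 and 12 months is answered by enrolled patients only.
   - The patient focus groups invite women who have taken part for at least 6 months, so barriers that arise from low digital skill are likely to be under-represented.
   - Digital literacy is a baseline item for enrolled patients (Box 1). It describes those who passed the screen and cannot describe those who did not.

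5. **Direction and size.** If women judged less digitally able would rate the portal less favourably, which is plausible but is not shown in the article, their removal shifts usability and satisfaction upwards. The size of the shift would depend on the fraction screened out and on how their ratings would have differed. Neither quantity is given, so no estimate is possible.

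6. **Can the screened-out group be counted?** Yes. The Reach section states: "Reasons for exclusion will be registered, as well as the number and reasons for drop-out during the study". It also starts from all patients whom the EHR shows to be finishing treatment and entering follow-up. The data needed to report the screen are therefore already planned.

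**The case against.** The strongest reply is that the Discussion already carries the caution that matters. It names patients who struggle with technology, the affected outcomes (usability and satisfaction) and the loss of representativeness. The study is a descriptive pilot, no analysis or sample size depends on the sentence, and the operative eligibility text is clear. One might also read the sentence charitably, as meaning only that no formal skills test is used.

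Much of this stands. The conclusion about representativeness is partly disclosed, and the fault lies in how the limitation is stated. The charitable reading does not rescue the sentence, however: an HCP's estimate of sufficiency, used as an entry criterion, is selection on digital skills whether or not a test is involved. A general caveat about volunteers does not tell the reader that a screen was applied first.

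A reader might infer four stronger points, and the article does not support them.

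- **That the results are set to be generalised to patients of any digital skill.** The Discussion itself warns against this.
- **That all selection is blamed on voluntariness.** Language and the single-centre setting are also named. Only the digital-skills selection is attributed to voluntariness alone.
- **That reach is inflated because screened-out women leave the denominator.** The Reach section takes the proportion over all patients entering follow-up. Table 3 is worded more loosely and mentions meeting the inclusion criteria, but it does not clearly set a denominator of eligible patients only. A numerical inflation factor would need both that denominator and an invented exclusion rate.
- **That criterion 2 ought to be removed.** With 26 of the 50 patients already included, this would change eligibility partway through recruitment, and criterion 4 would still select on much the same trait.

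**Conclusion.** The point holds as an internal contradiction with a consequence for what the study can conclude. The limitations deny a selection step that the eligibility criteria impose, on the trait closest to the main patient-reported outcomes. Usability, satisfaction and patient-reported barriers will describe women whom an HCP judged digitally able and who then chose CopA.

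That the results are conditional on this group follows directly from the text. That they are more favourable for this reason rests on the assumption that digitally less able women would have found the portal harder to use. How much more favourable cannot be determined from the article.

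This is a should-fix item. The existing caveat and the planned registration of exclusion reasons limit the harm, and the design can stay as it is.

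**What to change.** Make three changes.

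1. In the Discussion, replace the denial with a statement that patients are selected on HCP-estimated digital literacy and on ability to use the portal, and that voluntary participation may add further selection.
2. Restrict the usability and satisfaction conclusions to patients judged digitally able, and say that the patient-reported barriers come from the same group.
3. From the exclusion reasons already registered, report the number excluded under criteria 2 and 4 as a separate count. Calculate reach over all patients entering follow-up, as the Reach section describes, so that these women remain visible in the feasibility result.

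The cost is a few sentences and one extra line in the reach report. No new data collection is needed, provided that the registered reasons distinguish criteria 2 and 4 from the others. With recruitment under way, this is worth confirming now. The downside is a narrower stated conclusion.
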